## Abstract

**Background:**

In Brazil and other low- and middle-income countries, excess interventions in childbirth are associated with an increase in preterm and early-term births, contributing to stagnant morbidity and mortality of mothers and neonates. The fact that women often report a negative experience with vaginal childbirth, with physical pain and feelings of unsafety, neglect, or abuse, may explain the high acceptability of elective cesarean sections. The recognition of information needs and of the right to informed choice during childbirth can help change this reality. The internet has been the main source of health information, but its quality is highly variable.

**Objective:**

This study aimed to develop and evaluate an information and communication strategy through a smartphone app with respect to childbirth, to facilitate informed choices for access to safer and evidence-based care in the context of the COVID-19 pandemic.

**Methods:**

A randomized controlled trial, with 2 arms (intervention and control) and a closed, blind, parallel design, will be conducted with a smartphone app designed for behavior and opinion research in Brazil, with women of reproductive age previously registered on the app. After completing an entry questionnaire to verify the eligibility criteria and obtaining ethical consent, approximately 20,000 participants will be randomly allocated to the intervention and control groups at a 1:1 ratio. Participants allocated to the intervention group will be invited to engage in a digital information and communication strategy, which is designed to expand evidence-based knowledge on the advantages and disadvantages of options for labor and childbirth and the safety of the care processes. The information is based on the guidelines of the Ministry of Health and the World Health Organization for a positive childbirth experience and has been updated to include the new challenges and disruptions in maternity care within the context of the COVID-19 pandemic. The control group will receive information regarding disposable and reusable diapers as a placebo intervention. The groups will be compared in their responses in generating the birth plan and the entry and exit questionnaires, regarding responses less or more aligned with the guidelines for a positive childbirth experience. A qualitative component to map information needs is included.

**Results:**

The digital trial started recruiting participants in late October 2020, and data collection has been projected to be complete by December 2020.

**Conclusions:**

This study will evaluate an innovative intervention that has the potential to promote better communication between women and providers, such that they can make better choices using an approach suitable for use during the COVID-19 pandemic.

**Trial Registration:**

The Brazilian Clinical Trials Registry U1111-1255-8683; http://www.ensaiosclinicos.gov.br/rg/RBR-3g5f9f/

**International Registered Report Identifier (IRRID):**

PRR1-10.2196/25016

## Introduction

### Improvement of Maternal and Neonatal Health: a Permanent Challenge

Nationwide and worldwide studies have indicated, for many years, the need to act in order to reduce maternal and neonatal mortality, especially because a significant proportion of deaths can be avoided with adequate and timely assistance, considering the family planning continuum, prenatal care, childbirth assistance, and postnatal care [1-3]. Many sociohistorical, economic, and cultural factors interact, and the issue of maternal mortality remains poorly addressed, primarily in low- and middle-income countries such as Brazil. Thus, national and international stakeholders search for interventions that may contribute to significantly reduce maternal and neonatal mortality [1,3,4].

There have been advancements in the past decades in Brazil, with health professionals’ training, research, and improved access to prenatal care and childbirth assistance at health care facilities [5]. However, quality of care remains limited by non–evidence-based practices, within the context of increased use of inappropriate technology, which may be simultaneously harmful and costly [5]. At the health system level, in networks and facilities, women’s and families’ safety and well-being cannot be taken for granted, since recent studies have reported disrespectful practices in childbirth care [6,7], and in Brazil, infant and maternal mortalities have increased, raising public concern regarding maternity services [8]. In some scenarios, the uncertainties imposed by the COVID-19 pandemic in 2020 threaten the availability of medical resources and health care services, and studies have reported that Brazil has the highest COVID-19 mortality rates in the obstetric population [9,10].

### Maternal and Neonatal Morbidity and Mortality and Childbirth Care in Brazil

In Brazil, monitoring and regulation of obstetric interventions is limited. For example, the cesarean section rate remains as high as 55% since 2015, with rates of >80% in the private sector. This major surgery, when properly indicated and performed in a timely manner, protects the mother’s and the infant’s lives [11,12]. However, if performed without adequate reason, caesarean sections unnecessarily increase the risk to both mothers and neonates. In other words, unnecessary cesarian sections increase maternal and neonatal morbidity and mortality, as well as other negative outcomes, over the short and long term [13,14].

Several indicators show excess of interventions in childbirth care in Brazil, such as amniotomy (39.1%), fundal pressure (36.1%), episiotomy (53.5%), and oxytocin augmentation (36.4%) [5]. Simultaneously, pathological conditions are not adequately addressed, such as early identification of gestational hypertension, syphilis, and other infections during pregnancy. This is rather incompatible with current nationwide developments and with the presence of a universal health system.

Obstetric care can be characterized as a combination of “too little too late” with “too much too soon,” a reference to the insufficient and delayed use of necessary resources with the excessive and inopportune use of technology, potentially resulting in harm [15]. Abuse of unnecessary interventions has also been verified in the private sector, especially with high rates of caesarean sections. Furthermore, owing to the fact that in the private sector, a greater proportion of neonates are born in the early preterm period (37-39 weeks), neonatal admissions to intensive care units are more frequent, as are the cases of transient tachypnea, hypoglycemia, jaundice, and breastfeeding problems [5].

The main causes of neonatal death are prematurity (30.3%), congenital malformation (22.8%), and infection (18.5%), and mortality rates vary widely between regions. Late preterm infants (which accounts for 17.1% of all neonatal deaths) present a 9-fold greater chance of neonatal death compared to those born at term. In this context, it is recommended to improve the quality of prenatal care and to prevent iatrogenic prematurity, largely in cases of cesarean sections performed without technical indication [16]. Evidence- and rights-based care can reduce infant mortality by decreasing preventable neonatal deaths. This comprises deaths from intrapartum asphyxia, an important component of preventable neonatal deaths in the country [16].

### Resources to Increase Women’s Control Over Their Experience and Information Available on the Internet

During pregnancy, women seek information and want their needs to be heard, but educational materials, prenatal consultations, and support groups may not be sufficient or adequate [17]. Women can gather information from different sources such as their relatives, friends, the internet, and popular media [18-21]. Television shows and other popular media resources frequently resort to “experts” or other sources of information that are not scientifically validated. This influences women’s expectations and decisions regarding many aspects of their health, including childbirth fears and desires [19-23]. Incomplete information about cesarean sections is often disseminated, which “can lead women to underestimate important maternal and perinatal risks associated with this mode of parturition” [24]. A recent systematic review reported that there are few campaigns aimed at the general public to reduce the rates of cesarean sections [25].

The large volume of information available on the internet and its heterogeneity impact women's curiosity about certain topics, often to the detriment of others [26]. On Brazilian Portuguese webpages, the quality of information on cesarean sections varies from regular to poor, with low reliability and comprehensiveness [27]. This can cause anxiety among women [28], especially if the information is not discussed with health professionals [29] or confronted with other sources. To change this situation and contribute to increasing women's satisfaction, one possibility is to encourage the use of a birth plan, which improves their communication with health professionals and makes women more aware of their options [30].

In a systematic review in 2019, two trials observed that birth plans had a protective effect in promoting positive birth experiences in line with women’s perception. The quality of the studies was considered low, and the review concludes that more high-quality randomized studies are needed to assess the hypothesis that the use of the birth plan contributes to improving women’s satisfaction and promoting a more positive birth experience [31].

### Digital Technologies and Health Research

More than half of the world’s population has access to the Internet. In Brazil, a survey in June 2020 by the Getúlio Vargas Foundation of São Paulo [32] revealed that there are 190 million computers—including desktop, notebook, and tablet devices—currently in use in the country, which corresponds to 9 computers for every 10 inhabitants (90% per capita usage). Although approximately 25% of the population, especially the oldest and poorest individuals, remain digitally excluded, there are overall 234 million smartphones currently in use. In addition, considering notebook and tablet devices, there are 342 million portable devices currently in use; that is, 1.6 portable devices per inhabitant.

Throughout the 2010s, mobile phones spread digital health communication in low- and middle-income countries in South East Asia, sub-Saharan Africa, and Latin America, including Brazil. In the field of reproductive health, the establishment of opportunities for continuous communication, and complementary to institutional care for prenatal care, postpartum care and reproductive planning are associated with better perinatal outcomes [33,34], increased confidence and satisfaction with childbirth [35], increased knowledge of obstetric interventions such as uterine fundal pressure, episiotomy, and labor augmentation with oxytocin, increased perception of being better prepared for the childbirth experience [36], reduced anxiety [37], and reduced perinatal mortality [33]. Recent literature reviews revealed evidence of the effectiveness of digital interventions focused on pregnant and postpartum women, suggesting the need for more large-scale clinical trials [38,39].

To our knowledge, this will be a pioneering study, with population sampling in the country, assessing the preparation of a birth plan tool and women’s choices related to a safer and more positive childbirth experience.

### Emergence of the COVID-19 Pandemic: New Priorities Arise

On February 26, 2020, the first case of COVID-19 was reported in Brazil, and the disease was declared a pandemic by the World Health Organization on March 11, 2020. Since then, COVID-19 has monopolized the news and significantly modified the daily life of the population. Of note, Brazil ranks third worldwide with respect to the number of cases (>5 million) and deaths (>150,000) so far [40], while being amid a major political crisis. In addition, researchers in Brazil have observed an elevated COVID-19 mortality rate in the Brazilian obstetric population (12.7%), reporting 124 deaths among pregnant or postpartum women in June 2020, which is possibly the highest rate reported worldwide [9].

Innovative interventions have the potential to promote better communication between women in reproductive age and health care providers, such that they can make better choices. This study aims to develop and evaluate an information and communication strategy for a smartphone app on childbirth to facilitate informed choice for access to safer, more satisfactory, evidence-based assistance, in the context of the COVID-19 pandemic.

## Methods

### Study Design

This study is a randomized controlled trial, with 2 parallel arms (intervention and control) and a closed (only registered app users can participate) and blind design (only the participants are unaware of whether they are in the intervention or control arms). It is registered on the Brazilian Registry of Clinical Trials as “Communication intervention to improve informed choice at childbirth: a randomized controlled trial using digital technology in the context of the Covid-19 pandemic” with the World health Organization unique trial number U1111-1255-8683. The work is being conducted under a program supported by the Brazilian Ministry of Health (Programa de Apoio ao Desenvolvimento Institucional do Sistema Único de Saúde 25000.028646/2018-10).

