### Allocation and Randomization

Users will be recruited through the app, which is voluntarily installed by the user. Registrations are carried out organically, with no active screening for users and no advertising. Once registered, the new user answers questions related to his/her socioeconomic data. Missions will be sent to the profiles of users of all social classes (paired to represent the composition of the Brazilian population in the 5 regions of the country) and aged between 18 and 49 years.

Randomness in the sample is guaranteed in the program architecture of the missions, ensuring that those who undertake 1 mission will not be able to access the other mission, by blocking the mission ID through the execution of filters. On the app screen, the respondent sees only the name of the mission, with no indication of whether that participant is in the intervention or the control arm. To guarantee greater confidentiality and not induce interests or scams, we assigned the same name to the 2 missions: “Being a mother is making choices.” To balance the sample, the statistician team distributes the sample on the basis of the “n” defined for the study, thus generating a balance between the geographical region and economic class.

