### Outcomes

#### Primary Outcomes

The primary outcome measures (Table 1) will be the following:

Preference reported for the gestational outcome (for a healthy woman and neonate) the safety of which is determined on the basis of evidence: waiting for spontaneous onset of labor; waiting for the full 39 weeks; preference for vaginal childbirth; preference for cesarean delivery after labor; preference for elective cesarean delivery; or indifference.Differences between the responses in the elaboration of the birth plan, aligned with the information provided in the intervention, in accordance with the Ministry of Health guidelines.Knowledge of the COVID-19 pandemic’s impact in childbirth care and alternatives available.

**Table 1 table1:** Outcomes of interest and definitions.

Endpoints	Definitions
Engagement in the intervention	Proportion of invited women who finish the missions
Reduced interest in elective cesarean section	Reduction in the proportion of women who intend to schedule an elective cesarean section
Increased engagement in seeking protagonism or informed choice	Proportion of women who develop a birth plan
Knowledge of the safest, most effective options associated with a more positive experience	Safer, more effective choices associated with a more positive experience in the exit survey and the birth plan
Engagement or desire to elaborate and share the experience and concerns	Elaboration of a narrative of the experience, doubts, and expectations regarding childbirth
Knowledge of the options available during the COVID-19 pandemic	Responses compatible with the information offered

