### Data Management

For this study, a series of data management procedures will be implemented to ensure data protection, safety, privacy, and confidentiality. Data management will target the following three aspects: participant data treatment by the app’s parent company, relevant information transfer to researchers, and data set maintenance by all teams. It is worth mentioning that in compliance with security measures established by the general data protection law [50,51] and the resolutions of the National Council of Health for human experimentation [52], researchers will receive only the variables of interest for the study.

At the individual level, the collected data will be computed directly in the parent company’s system. This will include the following: verification of the individual's registration, deidentification of the data and separation of the population data for this study from the rest of the platform data, and the creation of an individual cloud to store the data for this specific study. Only the variables of interest in the deidentified data of the study participants will be used.

When accepting the app’s terms of use and privacy policy, all users have their data automatically pseudo-anonymized (ie, unidentifiable). These data include the following: personal data collected upon registration; complementary data captured during app use, such as a version of the smartphone’s operating system or device model; and all user responses during interventions.

At the level of database management by the researchers, the file will be initially processed within the app’s servers, where the raw data files will also be stored and will not be used for any purpose other than this study.

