#### Qualitative Analysis

Audio narratives (entry and exit questionnaires and birth plan) will be automatically transcribed and analyzed in accordance with Bardin thematic analysis [54], using the Qualitative Solutions Research NVivo software (version 12.0, QSR International). A priori categories will include the following: feeling informed to make choices, feeling physically and emotionally secure, factors influencing satisfaction or dissatisfaction, desire to do something differently, and information needs. A posteriori categories are expected to emerge, as experience is considered an expansive learning opportunity [55].

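### Blinding stops at the participants, leaving avoidable room for arm-aware classification of birth-plan and COVID-19 answers and arm-aware coding of narratives

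*Protocol article*

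**What the plan says.** All places are in the protocol article.

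- **Study Design** calls the trial blind and explains that "only the participants are unaware of whether they are in the intervention or control arms".
- **Allocation and Randomization** describes how this is done: both missions carry the same name, and the screen shows the name "with no indication of whether that participant is in the intervention or the control arm". It also says that "the statistician team distributes the sample on the basis of the" number defined for the study, balancing region and economic class.
- **Abstract, Methods** says the arms will be compared "regarding responses less or more aligned with the guidelines for a positive childbirth experience".
- **Primary Outcomes** includes differences in birth-plan responses, "aligned with the information provided in the intervention, in accordance with the Ministry of Health guidelines". Table 1 defines the COVID-19 knowledge endpoint as "Responses compatible with the information offered".
- **Qualitative Analysis** lists categories set beforehand and adds: "A posteriori categories are expected to emerge".
- **Data Management** has the app's parent company de-identify the data and states that "researchers will receive only the variables of interest for the study".

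**The concern.** Automatic capture by the app protects the recording of an answer. It does not protect the later decision on whether that answer counts as a success. If the decision is made, or revised, by someone who can see the arm, the grouping can drift, without intent, towards categories that separate the arms. The same applies to themes formed from narratives. Two of the three primary outcomes, birth-plan alignment and COVID-19 knowledge, rest on such a grouping. Data Monitoring and Auditing plans no monitoring committee and no independent audit. That is reasonable for a low-risk educational trial, but it leaves masking as one of the few remaining safeguards on this step.

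**Working it through.** The plan states no figure on this point, so the check is a reading of the sections against each other.

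**1. Who is masked.** Study Design says only the participants. Allocation and Randomization describes masking of the participant's screen and nothing else. De-identification under Data Management hides the person, not the arm. No section masks analysts, classifiers or coders. Because Study Design uses the word *only*, this is a stated choice and not a silence.

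**2. Which outcomes need a classification.**

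| Outcome (Primary Outcomes, Table 1) | Judgement needed after capture |
|---|---|
| Birth-plan responses aligned with the guidance | Yes: someone decides which answers are aligned |
| COVID-19 knowledge | Yes: someone decides which answers are compatible |
| Intention to schedule an elective cesarean | Little: a reported preference, counted |
| Missions finished; birth plan developed | Little: completion counts |
| Narrative endpoint | Little: defined as producing a narrative, not as its coded content |
| Thematic coding (Qualitative Analysis) | Yes, but in the qualitative component |

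**3. How much discretion remains.** Birth-plan alignment is tied to Ministry of Health guidelines, and COVID-19 knowledge to the content of the intervention. Both anchors narrow the choice. A single key fixed before the data are seen and applied to both arms would leave little room for bias. The article does not say whether such a key exists or when it is fixed. Emergent themes, by their nature, cannot be fixed before the narratives are read.

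**4. Precision, for scale only.** With the expected 10,000 per arm and the planned 99% intervals, the half-width for a difference in proportions is 2.576 × √(2p(1−p)/10,000). The prevalences are illustrative assumptions:

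- p = 0.10: 2.576 × √(0.18/10,000) = 0.011, or 1.1 points.
- p = 0.50: 2.576 × √(0.50/10,000) = 0.018, or 1.8 points.

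This is sampling precision, not an estimate of bias. It shows only that small differences will be detectable, so a small shift in grouping could matter.

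**5. Where masking could be placed.** Data Management already has a transfer at which variables are selected and de-identified. The arm can be held back there, after collection, with no change to recruitment, sample size, alpha or participant procedures.

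**The case against.** The strongest reply is that participant-only blinding is openly disclosed, that responses are captured automatically, that alignment refers to an external standard, and that the locking of a response key and the use of coded arm labels are commonly left to a SAP. Much of this stands. It is why the point is an improvement and not an error. It does not remove the point, because the article states who is masked and excludes everyone else.

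A reader might draw stronger conclusions that the documents do not support:

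- *That the team that built the intervention sorts the answers with the arm in view.* No section names the classifiers or the coders. Not masked is what the text supports.
- *That every primary outcome depends on the sorting.* The elective-cesarean proportion in Table 1, to which the sample-size section attaches its 20% impact, does not.
- *That narrative coding could change a between-arm result.* The abstract gives the qualitative component the task of mapping information needs, and Table 1 does not use coded themes. Entry-questionnaire narratives also precede the intervention.
- *That masking would be free.* The documents give no cost, and full masking may not be achievable.

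It is also fair to object that neutral labels alone are not enough. An analyst who sees codes X and Y still sees which groupings separate them; only the direction is hidden. The protection comes from withholding the arm altogether until the key is locked.

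**Conclusion.** The concern holds in limited form. The protocol confines blinding to participants. This leaves avoidable room for arm-aware decisions on birth-plan alignment, on COVID-19 knowledge and on narrative themes. The elective-cesarean proportion and the completion counts are little affected. The size of any bias cannot be derived from the documents. It would be small if a response key was fixed in advance, and could be material for the two classified primary outcomes if the key is settled or changed with the arm visible. The conclusion assumes that no masking of analysts or coders is specified in material not shown; the questionnaires sit in appendices that were not available. It is a cheap improvement, not a flaw that undermines the trial.

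**What to change.** State in the protocol that:

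1. At the transfer described under Data Management, the app company withholds the arm variable and the arm-specific mission content (childbirth or diaper questionnaires). It supplies a neutral mission-completion flag, because the engagement endpoint needs it.
2. The classification of birth-plan and COVID-19 answers and the narrative coding frame are locked before any arm information is released.
3. The primary analyses are then run with neutral arm codes, where possible by an analyst who did not handle allocation, and the key is released afterwards.

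The cost is one recode at an existing step. Masking will remain incomplete where exit or birth-plan narratives reveal the arm by their content, or where the statistician team that distributed the sample also analyses it. Both limits should be reported.
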